# Effects of concentrated long-chain omega-3 polyunsaturated fatty acid supplementation before radical prostatectomy on prostate cancer proliferation, inflammation, and quality of life: study protocol for a phase IIb, randomized, double-blind, placebo-controlled trial

**DOI:** 10.1186/s12885-017-3979-9

**Published:** 2018-01-10

**Keywords:** Prostate cancer, Omega-3, Proliferation, Inflammation, Quality of life

## Abstract

**Background:**

Prostate cancer is the most commonly diagnosed cancer in north-American men. Few dietary or lifestyle interventions have been tested to prevent prostate cancer progression. Omega-3 fatty acid supplementation represents a promising intervention for prostate cancer patients. The aim of the study is to evaluate the effects of long-chain omega-3 polyunsaturated fatty acids (LCn3), more precisely eicosapentaenoic acid monoacylglyceride (MAG-EPA) supplementation, on prostate cancer proliferation, inflammation mediators and quality of life among men who will undergo radical prostatectomy.

**Methods/design:**

We propose a phase IIb, randomized, double-blind placebo-controlled trial of MAG-EPA supplementation for 130 men who will undergo radical prostatectomy as treatment for a prostate cancer of Gleason score ≥ 7 in an academic cancer center in Quebec City. Participants will be randomized to 6 capsules of 625 mg of fish oil (MAG-EPA) per capsule containing 500 mg of EPA daily or to identically looking capsules of high oleic acid sunflower oil (HOSO) as placebo. The intervention begins 4 to 10 weeks prior to radical prostatectomy (baseline) and continues for one year after surgery. The primary endpoint is the proliferative index (Ki-67) measured in prostate cancer cells at radical prostatectomy. A secondary endpoint includes prostate tissue levels of inflammatory mediators (cytokines and proteins) at time of radical prostatectomy. Changes in blood levels of inflammatory mediators, relative to baseline levels, at time of radical prostatectomy and 12 months after radical prostatectomy will also be evaluated. Secondary endpoints also include important aspects of psychosocial functioning and quality of life such as depression, anxiety, sleep disturbances, fatigue, cognitive complaints and prostate cancer-specific quality of life domains. The changes in these outcomes, relative to baseline levels, will be evaluated at 3, 6, 9 and 12 months after radical prostatectomy.

**Discussion:**

The results from this trial will provide crucial information to clarify the role of omega-3 supplementation on prostate cancer proliferation, inflammation and quality of life.

**Trial registration:**

ClinicalTrials.gov Identifier: NCT02333435. Registered on December 17, 2014. Last updated September 6, 2016.

**Electronic supplementary material:**

The online version of this article (10.1186/s12885-017-3979-9) contains supplementary material, which is available to authorized users.

## Background

Prostate cancer (PCa) is a significant health problem worldwide. In Canada, 1 out of 8 men is expected to develop PCa in their lifetime and 1 in 27 will die from it [1]. Men diagnosed with intermediate risk PCa usually undergo radical prostatectomy (RP) or radiation therapy and have uncertain prognoses [1] and many side effects [2, 3]. For these patients, dietary and lifestyle interventions are considered promising strategies to improve health and quality of life [4].

### Omega-3 fatty acids

Long-chain omega-3 polyunsaturated fatty acids (LCn3), eicosapentaenoic acid (EPA) and docosahexanenoic acid (DHA), mainly found in seafood and fatty fish, might help lower PCa incidence and/or delay its progression [4–8]. However, some reviews reported no association [9–12] or mixed associations depending on LCn3 subtypes [13, 14]. It is important to note that observational studies are often limited by multiple sources of bias and the difficulty of estimating LCn3 intakes. LCn3 levels measured in red blood cells reflect the diet over the last 3 months [15]. However, studies that evaluated dietary LCn3 from biomarkers, assessed LCn3 in the plasma [9–11, 16–18], a measure that reflects the diet of the past few days [15]. Interestingly, we have recently measured LCn3 in the targeted prostate tissue during active surveillance of patients with a low-grade PCa. We observed a significant protective association between higher levels of EPA and a lower risk of progression to high-grade PCa [19].

### Proliferation

Nuclear Ki-67 is a protein expressed in all proliferative phases of the cell cycle [20–23].The proliferation rate of normal prostatic epithelial cells being very low, Ki-67 is mainly expressed in PCa cells and this proliferative index is considered an important prognostic factor for PCa patients [24–27]. A Phase II randomized controlled trial (RCT) comparing a low fat diet enriched with fish oil to a western diet, in 55 men, showed that prostatic Ki-67 expression was significantly reduced in the low-fat diet/fish oil group [28]. Flaxseed supplementation before RP was also associated with downregulation of Ki-67 in another RCT [29]. However, in these studies, proliferation was not the primary endpoint.

### Inflammation

Inflammation is a highly ordered, controlled and short-lived response to infection or injury. Tumors are often viewed as “wounds that do not heal” and can prevent the proper regulation of the resolution phase of inflammation, thus taking advantage of the inflammatory process for their own benefits. The microenvironment surrounding tumors can produce and secrete several cytokines and growth factors that promote proliferation and minimize apoptosis, thus driving carcinogenesis [30, 31]. Over-expression of several inflammatory mediators in prostate tissue (e.g. IL-1 [32, 33], IL-6 [32–34], TGF-β [35], TNF-α [32]) and blood (e.g. IL-6 [36], IL-7 [37] and IL-15 [37]) has been observed in PCa patients or PCa patients with progression.

LCn3, particularly EPA, have beneficial effects on systemic inflammation via modulation of the immune system, increase phagocytic activity, disruption of TLR signaling cascade and production of anti-inflammatory eicosanoids [38]. These effects are mediated by their incorporation into the plasmatic membrane. Previous studies have assessed the changes of only a limited range of systemic inflammatory mediators after omega-3 interventions, including IL-6 [39–43], IL-1β [40, 41, 43–46] and TNF-α [42–44]. However, the effects of nutritional interventions on prostate tissue inflammation has yet to be examined using a RCT design.

### Quality of life and psychosocial functioning

PCa and its treatment are associated with significant psychological distress. Large-scale epidemiological studies on psychological disorders in the context of PCa are sparse. Nonetheless, in a study conducted by our team in 861 patients treated for PCa, we found that 17.0% exhibited clinical levels of depression, while 23.7% of the patients had clinical levels of anxiety [47]. Moreover, we observed sexual difficulties, sleep impairments and fatigue in 70.5%, 31.9%, and 18.5% of the patients, respectively.

Epidemiological studies have shown associations between a greater annual fish intake and lower depression rates [48–50]. A RCT conducted in medical students (with no psychiatric disorder), comparing a 12-weeks LCn3 supplementation to a placebo, showed a 20% reduction of anxiety symptoms [51]. A recent study found no significant effect of omega-3 supplementation on sleep quality [52], while a study of 633 breast cancer survivors showed that a higher intake of omega-6 relative to omega-3 was associated with a higher risk of fatigue [53]. These questions remain to be investigated in PCa patients using a RCT.

### Rationale

Epidemiological studies point to a possible role of environmental factors, especially diet, in PCa incidence and progression. Evidence also suggests that an LCn3-rich diet may be beneficial to cancer patients through the modulation of cancer cell proliferation, inflammation, psychosocial functioning and quality of life. However, well conducted RCT assessing the effects of LCn3 on all these outcomes critical to PCa, are lacking. Therefore, a randomized, double-blind, placebo-controlled trial was initiated to examine the specific roles of LCn3 sub-type EPA on the biology and treatment consequences of PCa.

### Study objectives

We hypothesize that supplementation with EPA monoacylglyceride (MAG-EPA), beginning 6 weeks (range 4 to 10 weeks) before RP and for a year after RP, will have measurable effects on selected PCa outcomes. The specific objectives are as follows:

### Primary objective

To determine the effect of daily MAG-EPA supplementation compared to placebo, on the proliferative index (nuclear Ki-67 expression) of prostate cancer cells from the RP specimen.

### Secondary objectives

To determine the effect of the intervention, compared to placebo, on the targeted tissue expression of inflammatory mediators measured in the prostate tissue from the RP specimen.

To determine the effects of the intervention, compared to placebo, on blood levels, relative to baseline levels (before beginning of the intervention), of inflammatory mediators (cytokines and proteins), at the time of RP and one year after RP.

To assess the effect of the intervention, compared to placebo, on psychosocial functioning and quality of life outcomes, relative to baseline levels, at the time of RP and during the year following RP.

## Methods/design

### Trial design and setting

A phase IIb, randomized, double-blind, placebo-controlled trial will be conducted at the Centre Hospitalier Universitaire (CHU) de Québec – Université Laval, a supra-regional center with high surgical volume for urological cancer, particularly for prostate cancer (>350 RP per year). The parallel study design is presented in Fig. 1.

**Fig. 1 Fig1:**
[figure not shown]
Randomized Controlled Trial flow chart. 130 men diagnosed with intermediate-risk PCa treated by RP are being randomized either to LCn3 supplementation (MAG-EPA) or placebo. Intervention starts 6 weeks (acceptable range 4–10 weeks) before radical prostatectomy (RP) and ends 12 months after RP. PCa: Prostate cancer; Web-FFQ: online Food frequency questionnaire; QoL: Quality of life; PF: Psychosocial functioning; LCn3: Long chain omega-3 fatty acids; RP: Radical prostatectomy; MAG-EPA: Monoglycerides of eicosapentaenoic acid; HOSO: High oleic acid sunflower oil

### Recruitment

The study is advertised in the clinic with posters and the urologists will be reminded regularly of the study. At time of diagnosis, the urologist will discuss the different treatment options with the patient. When RP is chosen as part of the treatment, the patient will be informed of the study. Then, the research nurse will present the study information and the consent form. The patient will have the needed time to decide whether he wants to participate or not to the study.

### Patient population and eligibility criteria

#### Inclusion criteria

Patients must be 18 or older, give informed consent and have chosen RP for treatment of a PCa with a Gleason score ≥ 7.

#### Exclusion criteria

Patients are not eligible if they are intolerant or allergic to fish or sunflower seeds or if they have a diagnosis of bipolar disorder.

#### Washout period

Patients already taking omega-3 supplements can participate after a washout period of at least 8 weeks before randomization. Other dietary supplements must be stopped before randomization.

### Randomization/concealment/blinding

Patients will be randomized to the intervention or placebo group 6 weeks (acceptable range 4 to 10 weeks) prior to RP. Randomization will take place at the preoperative appointment or an appointment taken specifically for the study. The randomization process will consist of a computer-generated random listing of the treatment arm using a 1:1 allocation. The randomization will be generated by the Clinical research oncology pharmacy, using permuted random blocks of 2 to 8. Patient allocation information will be kept in a binder in a locked room of the pharmacy for the entire study period. Patients, as well as all study personnel, including outcome assessors, and medical doctors will be blinded to treatment allocation and block sizes.

### Intervention

Participants assigned to the intervention will receive, for each intervention day, 6 capsules of 625 mg of fish oil (MAG-EPA) per capsule. The supplementation is highly concentrated in EPA giving a total dosage of 3 g of EPA daily. The novel fish oil formulation is based on monoglycerides containing 89% of LCn3, with 80% EPA. It presents a unique ratio of EPA/DHA of more than 10. Most of the available products have a ratio of less than 2. It also contains approximately 3% omega-6, 3% monounsaturated and 3% saturated fatty acids and have a less pronounced “fishy” taste compared to usual preparations.

Participants assigned to the placebo group will receive, for each intervention day, 6 capsules of identical appearance containing high oleic acid sunflower oil (HOSO). These capsules contain 82% of omega-9 and are poor in omega-3 or omega-6. This is a biologically neutral oil and has thus been used as a placebo in at least 3 LCn3 RCTs [43, 54, 55].

Capsules, for intervention and placebo, are prepared by SCF Pharma, Ste-Luce (Qc), and will be odorless and of identical appearance for both groups. Health Canada approved the RCT protocol and the products used for the intervention and placebo arms.

For both groups, the intervention will start 6 weeks (range 4 to 10 weeks) prior to RP and will be pursued for one year after RP. At randomization, patients receive, by the pharmacy personnel, the amount needed until their first follow-up visit, three months after surgery. They then receive, at every follow-up visit, the amount needed for the next three months until the end of follow-up.

The follow-up and care received by the patients will be the same for both groups.

### Concomitant medication

Health Canada does not have any contraindication for the proposed daily dose [56]. Thus, there will be no contraindication concerning other medications taken by the patients and they will be asked to follow their usual regimen. Medications’ usage will be carefully documented at the initial and subsequent visits.

### Data collection and follow-up

The assessment schedule of the study is presented in Table 1. Patients will be assessed at randomization, surgery and every 3 months until one year after RP.

**Table 1 Tab1:** Data collection schedule

	Initial visit	Randomization	RP	Post-RP follow-up			
	Eligibility	Intervention (baseline - V0)	V1	V2 3 mo	V3 6 mo	V4 9 mo	V5 12 mo
Consent		X					
Medical history and health behaviors		X					
Concomitant medication/symptom evaluation		X		X	X	X	X
Consultation with uro-oncologist	X			X*	X*	X*	X*
Blood sample including total PSA and lipid profile		X	X	X	X	X	X
Digital rectal exam and urine sample		X					
Radical prostatectomy (RP)			X				
Food frequency questionnaire - FFQ online		X					X
Prostate specific quality of life (IPSS and EPIC-26)		X		X	X	X	X
Hospital Anxiety and Depression Scale (HADS)		X		X	X	X	X
Quality of life (sleep quality, fatigue, cognitive functioning) (ISI, ISF, FACT-COG V3)		X		X	X	X	X
General health and wellbeing (SF-36)		X		X	X	X	X
Fear of recurrence (FCRI)		X		X	X	X	X
Self-reported sleep diary		X	X	X	X	X	X
Therapeutic expectation questionnaire				X			X
Anthropometric measurements^¶^		X					X
Vital signs^£^		X		X	X	X	X

RP: Radical Prostatectomy; V: visit; mo: months; PSA: Prostate Specific Antigen; IPSS: International Prostate Symptoms Score; EPIC: Expanded Prostate Index Composite; HADS: Hospital Anxiety and Depression Scale; ISI: Insomnia Severity Index; FSI: Fatigue Symptoms Inventory; Fatigue Symptoms Inventory and Functional Assessment of Cancer Therapy – Cognitive Function (FACT-COGv3); SF-36: Short-Form Health Survey; FCRI: Fear of Recurrence Inventory

*The consultation with the urologist might be on a different day but at the same period

^¶^Height, weight, hip and waist circumference, body fat measured by skinfold caliper

^£^Temperature, blood pressure and pulse

### Prostate tissue harvesting and biological specimens

At the time of RP, immediately after surgical removal, the prostate will be kept cold (4 °C) and transferred to the pathology unit for evaluation. A complete cross-section of the prostate will be harvested by the pathologist. The cross-section will be divided in four specific quadrants before Optimal cutting temperature (OCT) compound freezing procedure. A small portion of each quadrant (approximately 10 mg) will be harvested from the cross-section and snap frozen separately. All prostate tissues are stored at −80 °C.

50 ml of blood will be collected at indicated time-points (Table 1). Plasma, buffy coat, red blood cells, and serum will be processed from 35 mL of blood collected. All samples will be stored at −80 °C. Urine post-digital rectal examination will be collected at initial visit and stored in several buffers at −80 °C.

Procedures used in this research followed the Standard operating procedures (SOPs) of the Canadian Tissue Repository Network (CTRNet). All biological specimens will be stored at the Centre de recherche du CHU de Québec – Université Laval – L’Hôtel-Dieu de Québec hospital and all patients will have provided consent for long-term storage of their tissue.

Detailed information about samples, volume collected and aliquot is provided in the (see Additional file 1: Table S1).

### Outcomes

#### Primary outcome

The primary outcome is cancer proliferation. After immunostaining for Ki-67, slides will be scanned using an automated slide scanner and the proportion of cancer cells with positive nuclear staining will be automatically quantified using algorithms we previously developed with the Calopix (Tribvn) software [27]. Initial results in PCa tissue from RP specimens at our institution showed a linear correlation between automated quantification and visual evaluation [27]. This PCa proliferative index was also an independent predictor of prostate cancer specific mortality, making this outcome clinically relevant.

#### Secondary outcomes

Many inflammation mediators (Il-2, IL-8, IL-10, IL-12, IFN-γ, to name a few) will be measured in the prostatic tissue and in circulation using a Bio-plex Precision Pro kit (Bio-Rad, Toronto, On). The limit of sensitivity (LoS) ranges from 0.2–2.7 pg/mL, allowing for greater probability of detecting the cytokines of interest, if expressed, than usual multiplexing kits (LoS of 2–5 pg/mL).

Prostate specific aspects of quality of life is assessed using the International Prostate Symptoms Score (IPSS) and the Expanded Prostate Index Composite score (EPIC-26) for which the French-Canadian version has been validated [57, 58]. The IPSS contains 7 questions concerning lower urinary tract symptoms for which severity is scored on a 0–5 points scale. It also contains one quality of life item scored on a scale ranging from 0 to 6. EPIC-26 contains 5 quality of life PCa-specific domains: urinary incontinence, urinary irritation/obstruction, bowel, vitality/hormonal, and sexual function. Each domain is scored on a scale from 0 to 100.

Anxiety and depression are assessed using the French-Canadian version of the Hospital Anxiety and Depression Scale (HADS) for which we observed excellent internal consistency and test-retest reliability [59]. The questionnaire includes 14 items scored on a scale range from 0 to 3, with 7 items assessing anxiety and 7 items assessing depression.

Fatigue related quality of life is assessed using French versions of the Insomnia Severity Index (ISI) [60] and the Fatigue Symptoms Inventory (FSI) [61]. The ISI enquires about sleep quality over the past two weeks and contains 7 items scored on a 0 to 4 scale. Good psychometric properties have been reported [62]. The FSI questionnaire assesses, for the past week, fatigue intensity (4 items), fatigue duration (2 items) and how fatigue interfered with quality of life (7 items). The questionnaire exhibited high internal consistency and construct validity [61].

Cognitive function was also evaluated with the Functional Assessment of Cancer Therapy – Cognitive Function (FACT-COG v3) [63]. The questionnaire contains 37 items covering 4 subscales. The subscale includes Perceived cognitive impairments, Comments from others, Perceived cognitive abilities and Impact on quality of life. Each item is scored on a 5-points Likert scale ranging with a range of 0 to 4. This tool also showed high consistency and validity [63].

To assess cancer-specific anxiety, fear of recurrence is evaluated using the 9 items of the severity subscale of the Fear of Cancer Recurrence Inventory (FCRI) which was validated in french [64]. The items are scored from 0 to 4 and assess the presence, frequency and intensity of thoughts associated with cancer recurrence.

Finally, general wellbeing is evaluated using the French version of the Short-Form Health Survey, SF-36, (SF-36v2 Standard, Canada (French) Version 2.0) [65].

### Confounding variables

Potential confounders will be measured at baseline, before the beginning of the intervention. Age, anthropometry, medical history, cancer stage, clinical and pathological grade (Gleason), alcohol and tobacco use will be assessed.

Physical activity for a typical 7-day period will also be assessed at baseline by the Godin Leisure-Time Exercise Questionnaire [66]. The questionnaire contains 3 items assessing the number of times engaging in mild, moderate and strenuous exercises for at least 15 min. One item evaluates the number of times one engages in any activity long enough to work up a sweat.

Dietary intake in the past month will be measured using a web-based self-administered food frequency questionnaire (web-FFQ), which contains 136 questions and 40 sub-questions covering 8 food categories including the four groups of the Canadian Food Guide. The questionnaire has been specifically developed for the population of Quebec and validated in healthy men [67]. We also specifically validated the assessment of omega-3 intake in a population of PCa patients [68]. Dietary intake will be assessed at baseline and 12 months post-RP.

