### Statistical analyses

#### Primary outcome

The average proportion of cells expressing Ki-67 in each group will be compared, using the t-test, after transformation of the data if the population is not normally distributed. The Wilcoxon rank sum test will be used if observations are not normally distributed after transformation procedures. Multivariable linear regression will be carried out in the event of unbalanced distributions of important baseline characteristics such as cancer grade and stage, age, baseline inflammatory levels, diet or health behaviors. The intervention leading to the primary outcome is of a relatively short duration (4–10 weeks) and since almost all recruited patients are expected to undergo prostatectomy, few missing data are expected. The analyses will include all randomized patients for whom a ki-67 is measurable.

A *per protocol* analysis will also be carried out as exploratory analyses. These analyses will include participants with a measurable ki-67 and who will have taken at least 80% of intervention or placebo doses.

For all analyses, bilateral *p*-values of less than 0.05 will be considered statistically significant.

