#### Secondary outcomes

For the secondary outcome pertaining to prostatic levels of inflammation mediators, the t-tests (or Wilcoxon rank-sum test) will be used to compare levels across groups.

Blood levels of inflammation biomarkers as well as outcomes concerning quality of life are measured at multiple time points. For these analyses, linear mixed models, to take into account for multiple measurements, will be performed.

Confounding factors will also be taken into account in the analyses in the case of unbalanced distribution between groups.

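### Pathological Gleason grade is listed as a pre-intervention confounder although it is read after 4 to 10 weeks of treatment, so the conditional adjusted analyses could adjust for a post-randomisation variable

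*Protocol article*

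**What the plan says.** The section Confounding variables opens with a timing rule: "Potential confounders will be measured at baseline, before the beginning of the intervention". The next sentence gives the list: "Age, anthropometry, medical history, cancer stage, clinical and pathological grade (Gleason), alcohol and tobacco use will be assessed".

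The analysis sections use such variables conditionally. For Ki-67, the section Statistical analyses, Primary outcome, plans a t-test (Wilcoxon if normality fails). It adds multivariable linear regression in the event of "unbalanced distributions of important baseline characteristics such as cancer grade and stage, age, baseline inflammatory levels, diet or health behaviors". For the secondary outcomes the rule is: "Confounding factors will also be taken into account in the analyses in the case of unbalanced distribution between groups".

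The timing of the surgical specimen is given elsewhere. Under Intervention, "the intervention will start 6 weeks (range 4 to 10 weeks) prior to RP and will be pursued for one year after RP". Under Prostate tissue harvesting and biological specimens, "immediately after surgical removal, the prostate will be kept cold (4 °C) and transferred to the pathology unit for evaluation". A grade also exists before treatment, because the inclusion criteria require that patients "have chosen RP for treatment of a PCa with a Gleason score ≥ 7".

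**The concern.** Two consecutive sentences conflict. A grade read from the removed prostate cannot have been measured before an intervention that starts weeks before its removal. Pathological grade is a post-randomisation variable, and it comes from the same surgical specimen as the primary Ki-67 measurement.

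The conflict matters because the list feeds an adjustment rule that is triggered by imbalance. For a variable fixed before randomisation, an imbalance is chance. For a variable read after treatment, a difference between arms may be chance or may be an effect of treatment. If the supplement lowered surgical grade, that difference would look like an imbalance, call for adjustment, and take part of the treatment effect out of the adjusted estimate. The tissue inflammatory mediators, from the same specimen, are exposed in the same way through the rule for secondary outcomes.

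**Working it through.** **1. Order of events.**

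| Item | When known | Source in the protocol article |
|---|---|---|
| Gleason score at entry | Before randomisation | Inclusion criteria |
| Confounders, as stated | Before the intervention | Confounding variables |
| Start of capsules | 4 to 10 weeks before surgery | Intervention |
| Prostate sent to pathology | After removal | Prostate tissue harvesting and biological specimens |
| Ki-67 | From the surgical specimen | Primary objective |

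The article does not define pathological grade. Set beside clinical grade, and with the prostate reaching pathology only after removal, it has little other meaning than the specimen grade. It then falls after randomisation and fails the section's own timing rule.

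**2. The plan's own figure.** Inputs from Sample size calculation: coefficient of variation 0.4, ratio 0.8, two-sided alpha 0.05, power 90%.

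- SD of log Ki-67 = sqrt(ln(1 + 0.4²)) = sqrt(0.1484) = 0.385
- Effect = |ln 0.8| = 0.223, so d = 0.223 / 0.385 = 0.579
- n per group = 2 × (1.960 + 1.282)² × 0.1484 / 0.223² = 62.6, rounded up to 63; total 126
- With 3% dropout: 126 / 0.97 = 129.9, rounded up to 130

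The stated 63 per group, 126 and 130 are reproduced. Nothing in this point changes them.

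**3. Possible size of the attenuation.** The documents give neither the effect of treatment on grade nor the effect of grade on Ki-67, so the following are assumptions: 40% of placebo specimens are high grade; high grade raises log Ki-67 by 0.2 or 0.4; the true total ratio is 0.80; treatment lowers the high-grade share by 0, 5, 10 or 20 percentage points. The ratio expected after adjusting for surgical grade is

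exp(ln 0.8 + fall in share × effect of grade).

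For example, exp(−0.223 + 0.10 × 0.4) = exp(−0.183) = 0.833. Power is from 3,000 simulated trials per row, 63 per group, regressing log Ki-67 on arm and surgical grade.

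| Fall in high-grade share | Effect of grade on log Ki-67 | Expected adjusted ratio | Power, adjusted |
|---|---|---|---|
| 0 points | 0.2 | 0.800 | 0.905 |
| 0 points | 0.4 | 0.800 | 0.960 |
| 5 points | 0.2 | 0.808 | 0.890 |
| 5 points | 0.4 | 0.816 | 0.912 |
| 10 points | 0.2 | 0.816 | 0.850 |
| 10 points | 0.4 | 0.833 | 0.863 |
| 20 points | 0.2 | 0.833 | 0.766 |
| 20 points | 0.4 | 0.867 | 0.653 |

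The simulated adjusted ratios agree with the formula to within 0.002. The unadjusted test stayed at a ratio of about 0.80 with power 0.88 to 0.91 throughout. Every simulated trial was adjusted, whether or not an imbalance would have triggered it, so the table shows what happens once the surgical grade is in the model.

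**4. Reading the table.** With no effect on grade there is no attenuation, and adjustment gains a little power. With a fall of 5 points the loss is negligible. A large loss needs a fall of about 20 points within 4 to 10 weeks.

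**The case against.** The strongest reply is that the plan never says pathological grade will be a model covariate. The list states what is collected, and the same section also describes diet at 12 months after surgery, so a place there does not by itself put a variable in the model. The primary rule refers to baseline characteristics, and every patient has an entry grade, so the pre-treatment grade is a natural reading. The exact covariate list may also sit in an analysis plan that is not shown.

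Much of this stands. Use of the surgical grade is permitted, not certain. What it does not remove is that the article itself places pathological grade among the confounders it calls baseline, so the word baseline in the primary rule does not keep it out. The rule for secondary outcomes does not use the word at all. This is a stated rule that conflicts with the stated timing, not a detail left for later.

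A reader might go further and infer that the primary Ki-67 result will be biased. The documents do not support that. The main comparison is the unadjusted test. Bias in the adjusted estimate needs three things together: the imbalance trigger fires, the surgical grade is the one chosen, and treatment has shifted it. The article reports an observational association between prostate EPA levels and progression to high-grade disease under active surveillance. That stops one from assuming that grade is unaffected, but it does not show a change within 4 to 10 weeks.

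A reader might also infer that pathological stage is listed. It is not; the text says only cancer stage, which is ambiguous in the same way.

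**Conclusion.** The point holds as a moderate one. The list and its timing rule contradict each other, and the adjustment rules for primary and secondary outcomes admit a post-randomisation covariate that could trigger its own adjustment. The exposure is confined to the conditional adjusted analyses.

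The size is unknown from the documents. Under the assumed inputs above, an adjusted ratio of about 0.81 to 0.87 in place of 0.80 would go with a fall of 5 to 20 points in high-grade share, and power for the adjusted test would range from about 0.91 down to 0.65. These figures illustrate the mechanism and are not predictions. If grade is unaffected, the attenuation is zero. A must-fix rating would need evidence that treatment moves grade, or a main analysis that depends on the adjustment; the documents contain neither.

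**What to change.** - Remove pathological grade from the confounder list, so that the list agrees with its own timing rule.
- State, for primary and secondary outcomes alike, that the grade and stage used for adjustment are the pre-randomisation (biopsy or clinical) values.
- Report pathological grade by arm descriptively only, neither as a covariate nor as a trigger for adjustment.

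The cost is a sentence or two. The entry criterion already requires a pre-treatment grade, and the sample size stays at 126, or 130 with dropout. The downside is precision: surgical grade may predict Ki-67 better than the pre-treatment grade. In the rows with no treatment effect on grade, adjusting for it gave power of 0.905 to 0.960, against about 0.89 unadjusted, so the possible loss is modest and leaves the planned t-test as it is. Enrolment closed in June 2017 and data collection was expected to end in August 2018. The change should therefore be dated and made before the arms are compared.
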